## Abstract

**Background:**

Postpartum mood and anxiety disorders (PMADs) are higher among pregnant military service women (26%) and military spouses (12.2%) compared to the civilian population (10%-15%). This is partly due to military-specific factors, including deployment, which are known to increase risk. Important risk factors for PMADs include sleep disturbances, defined as sleep deprivation, insomnia, or poor sleep quality, which are more are common among military-affiliated pregnant women.

**Objective:**

This study describes a protocol for a new randomized controlled trial that aims to ameliorate the risk for PMADs through improving infant sleep or maternal sleep during the first 6 postdelivery months in a sample of military-affiliated women.

**Methods:**

This study is a 6-month, parallel-arm, randomized controlled trial. Pregnant women (N=342) in the third trimester will be randomized at 1:1 ratio to use a smart bassinet (SB) or a standard commercially available bassinet (HALO BassiNest Swivel Sleeper 3.0; traditional bassinet [TB]) for up to 6 months after delivery. Participants will have their infants sleep in the bassinet, complete monthly web-based questionnaires, and record sleep data with diary and actigraphy for both the participants and their infants for 1 week each postpartum month. Blood samples will also be collected at baseline (late pregnancy) and at 3 months and 6 months post partum to assess immune functioning. The primary outcomes for this study will be postpartum mood (depressive and anxiety symptoms) and infant and maternal sleep. In addition, we are evaluating whether SB has a significant impact on immune functioning—a marker that physiologically connects sleep and mood symptoms.

**Results:**

Recruitment for this study began in January 2025. Six separate mixed 2 (treatment vs control) × 6 (assessment period) multivariate analysis of variance and analysis of variance models will be conducted to test the hypotheses that SB will have a greater impact on infant and maternal sleep than TB, SB will be associated with a greater reduction in postpartum mood symptoms than TB, and immune system function will be less dysregulated in birthing individuals using SB compared to those using TB. Lastly, we will evaluate whether the elevated risk demonstrated by previously identified postpartum depression epigenetic biomarkers in the *TTC9B* and *HP1BP3* genes can be modified with an SB. We hypothesize that the elevated risk will be reduced in SB compared to that in TB.

**Conclusions:**

At the conclusion of this project, we will have gained a thorough understanding of the capability of SB to positively affect infant and maternal sleep compared to the traditional sleep arrangement and its impact on maternal mood through 6 months post partum in military-affiliated women. The promotion of sleep health in both mothers and infants may be an accessible and amenable method to prevent PMADs.

**Trial Registration:**

ClinicalTrials.gov NCT06544941; https://clinicaltrials.gov/study/NCT06544941

**International Registered Report Identifier (IRRID):**

PRR1-10.2196/66439

## Introduction

Postpartum mood and anxiety disorders (PMADs) are the most common and disabling complications of childbearing. They are often underdiagnosed and undertreated [1]. PMADs are recognized to seriously affect both mother and baby [2,3]. In fact, mental health conditions are a leading contributor to maternal morbidity, with suicide as a major cause of postpartum death. According to the Department of Defense, the number of females in the US military constituted 17.3% of the total force in 2021 [4]. Research indicates that the rate of PMADs in active-duty women can range from 20% to 26% [5-7], with slightly lower rates among military spouses at around 12.2%. Although these rates are similar to that reported in the civilian population (~10%-15%) [8-10], when other factors such as deployment are considered, the rates vary dramatically, reaching as high as 50% [11-16]. Women with spouses who are deployed have more frequent diagnoses of depressive disorders, sleep disorders, anxiety, acute stress reactions, and adjustment disorders compared to women without a deployed spouse. Despite these elevated risks, this segment of our population has been insufficiently evaluated as it pertains to PMAD risk and warrants further attention.

It is well appreciated that sleep disturbance is associated with both new and recurrent depressive and anxiety episodes in all populations, especially perinatal women [17-22]. Sleep disturbance often precedes the development of mood disorders [23,24]. Indeed, sleep issues lasting for at least 2 weeks increase the risk for the future development of mood disorders [25,26] and are a criterion for the diagnosis of depression in the Diagnostic and Statistical Manual of Mental Health Disorders, Fifth Edition, Text Revision (eg, major depressive disorder) [27]. Sleep disturbances, both in prevalence and severity, in military-affiliated women extend beyond what civilian women experience. Active-duty service members and their spouses experience unique stressors that often exacerbate sleep issues [28,29]. Despite this, there are limited empirical data regarding sleep disturbances among military-affiliated women.

Infant sleep problems further contribute to significant maternal sleep issues [30-32] and maternal mental health consequences, regardless of the mothers’ depression history [32-34]. Mothers who report poor infant sleep behavior have significantly more depressive symptoms than mothers who report good infant sleep [35-37]. There is some evidence that maternal sleep quality is a mediator of this relationship [35]. Persistent, rather than transient, infant sleep issues contribute to maternal depression, poor sleep, and poor family functioning well into toddlerhood [33,38,39]. We propose that focusing and intervening on infant sleep is a viable pathway to improve maternal sleep and well-being.

Here, we describe the protocol for a randomized controlled trial (RCT; Clinical Trials.gov CT94252410690; Sleep Health and Mood in Newly Expectant Military Mothers [SHINE]) with the following aims.

Determine whether the use of a smart bassinet (SB) augments infant sleep and improves maternal sleep during the first 6 months post partum compared to the use of a traditional bassinet (TB). (1) Hypothesis 1a: Infants who sleep in SB will have better sleep (ie, diary and Brief Infant Sleep Questionnaire as maternally reported) [40] than those who sleep in TB. Outcomes will include maternally reported sleep duration, awakenings, as well as objectively assessed (actigraphy) wake after sleep onset and sleep onset latency. (2) Hypothesis 1b: Mothers of infants who sleep in SB will have better subjectively reported (ie, diary and Pittsburgh Sleep Quality Index) and objectively assessed (actigraphy) sleep compared to those of infants who sleep in TB. Outcomes will be the same as those for infants.Determine the effect of SB on maternal postpartum depressive and anxiety symptoms and evaluate the model that the association between SB and postpartum depressive symptoms is mediated by both infant and maternal sleep. (1) Hypothesis 2a: Mothers of infants who sleep in SB will have fewer postpartum depressive symptoms over time (ie, Edinburgh Postnatal Depression Scale) compared to those of infants who sleep in TB. (2) Hypothesis 2b: SB improves infant sleep, which then predicts better maternal sleep, and thereby predicts lower maternal depressive symptoms.Compare the trajectory of immune system function from late pregnancy through post partum between participants with and without PMADs and between SB and TB groups. (1) Hypothesis 3a: Peripheral cytokines, immune cells, and stimulated cytokine profiles of women with PMADs assessed in late pregnancy and at 3 and 6 months post partum will indicate greater innate immune activity compared to those of women without PMADs. (2) Hypothesis 3b: Mothers of infants who sleep in SB will exhibit lesser innate immune dysfunction than mothers of infants who sleep in TB.Exploratory aim: Evaluate whether the elevated risk demonstrated by previously identified PMAD epigenetic biomarkers at the TTC9B and HP1BP3 genes can be modified by using an SB. We hypothesize that the elevated risk will be reduced in the SB group compared to that in the TB group.

## Methods

### Study Design

This study is a 2-arm, parallel-group RCT. Participants will be randomized at 1:1 ratio to either SB group or TB group. Outcomes are assessed at 7 timepoints (Figure 1): late pregnancy (P3) and in postpartum months 1-6 (M1-M6).

**Figure 1 figure1:**
[figure not shown]
Flowchart in this study. BISQ: Brief Infant Sleep Questionnaire; EPDS: Edinburgh Postnatal Depression Scale; ESS: Epworth Sleepiness Scale; FFS: Flinders Fatigue Scale; IBQ-R: Infant Behavior Questionnaire-Revised; ISQ: Insomnia Symptom Questionnaire; PSQI: Pittsburgh Sleep Quality Index; SCID: Structured Clinical Interview for Diagnostic and Statistical Manual of Mental Disorders-5.

### Ethics Approval

This study has been approved by the institutional review board of the University of Colorado Colorado Springs (#2024-071) and the Office of Human Research Oversight (US Army Medical Research and Development Command). The SHINE trial was previously registered with Clinical Trials.gov (CT94252410690). This protocol follows recommendations from CONSORT (Consolidated Standards of Reporting Trials) 2010 statement checklist (Multimedia Appendix 1) and guide [41]. All participants will be required to provide informed written consent prior to enrollment. Participation is completely voluntary, and the participant has the right to withdraw at any time. All participants will be assigned a 6-digit ID number to be used so that all data collected will be deidentified. Participants will be compensated for their time. There are 7 timepoints in this study. At baseline (late pregnancy), participants will be compensated US $100; at postpartum months 1, 2, 4, and 5, they will be compensated US $50 for data collection, and at postpartum months 3 and 6, they will be compensated US $100. At baseline and at postpartum months 3 and 6, they will provide a blood sample.

### Participants

At the time of recruitment (P3) (third trimester), participants will complete a screening survey to determine their eligibility. Eligible pregnant women (N=342) will be recruited nationwide. The inclusion criteria were pregnant military-affiliated individuals with a singleton gestation; age 18-45 years; ability to communicate in English during the screening process; access to a computer, smartphone, or tablet with internet service; willing to use the bassinet they are randomized to; and willing to travel to a local Quest Diagnostics (an insert description) for blood draw. The exclusion criteria were presence of a depressive or anxiety disorder assessed over videoconference using the Structured Clinical Interview for Diagnostic and Statistical Manual of Mental Disorders-5-Clinical Version mood disorders section [42]; current active suicidal ideation, medical or psychiatric instability, or active substance abuse or dependence during the last 90 days; plans to co-sleep with infant; younger than 18 years or older than 45 years; multiple gestations; type 1 diabetes; congenital fetal anomalies; tobacco use (current); self-reported, untreated comorbid sleep disorders, including narcolepsy, periodic leg movement disorder, or obstructive sleep apnea; and current use of psychotropic or sleep medications.

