#### Telephone Interview and Screening

Participants who meet initial inclusion criteria and have completed the consent and baseline questionnaires will be contacted for a telephone interview to assess further eligibility. The interview will contain items of the Structured Clinical Interview for Diagnostic and Statistical Manual of Mental Disorders-5-Clinical Version [42] and the Structured Clinical Interview for Sleep Disorders-Revised [43]. Eligible participants will be randomly assigned to either SB group or TB group. The SB will be shipped to the participants and returned after M6 at no expense to them. TB group participants will be shipped a standard bassinet (HALO BassiNest Swivel Sleeper) to keep. Mother-infant dyads (up to N=342) will be randomly assigned to conditions by using a random number generating program found on a widely used and reputable website [44]. We will perform 1:1 randomization. Variability in the length of bassinet usage may be impacted by size of infant, parental preference, or infant temperament. However, data will be collected through 6 months post partum.

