**Maternal screening measures**														
	Consent/inclusion/exclusion	✓												
	Demographics	✓												
	SCID^b^ depression module/sleep SCID	✓												
	Infant assessments													
	Actigraphy			✓		✓		✓		✓		✓		✓
	Brief Infant Sleep Questionnaire			✓		✓		✓		✓		✓		✓
	Infant Behavior Questionnaire-Revised			✓		✓		✓		✓		✓		✓
	Baby Cry/Fuss chart			✓		✓		✓		✓		✓		✓

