#### Primary Maternal Assessments

The Consensus Sleep Diary [50] will collect subjective sleep, while actigraphy will be contemporaneously used to derive objective sleep data. The Pittsburgh Sleep Quality Index [51] will measure habitual sleep quality. The Edinburgh Postnatal Depression Scale [52,53] will be used to assess changes in the depressive symptoms over time. The Generalized Anxiety Disorder Scale-7 items [54] and the Perinatal Anxiety Screening Scale [55] will be used to assess anxiety symptoms over time.

Participants will have their blood drawn (up to 20 mL) at enrollment, 3 months post partum, and 6 months post partum at a Quest Diagnostics laboratory near them (Figure 1). Briefly, blood collection kits with ethylenediaminetetraacetic acid tubes will be mailed to participants with a requisition form and a laboratory directive (from Quest) that provides the Quest Diagnostics Patient Service Center instructions on how to collect and process the study kit. Blood samples will be shipped in a temperature-controlled fashion to the Psychoneuroimmunology in Pregnancy & Postpartum (PIPPI) laboratory at Weill Cornell Medical College for analysis. Measurements of circulating cytokines, stimulated cell assays, and flow cytometry analysis will be conducted to evaluate the role of immune dysregulation.

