### Limitations

This study will, however, have important limitations that warrant discussion. The study goal is to determine whether SB can prevent or reduce the reoccurrence of PMADs and not for use as an active treatment. Hence, we chose to exclude participants with active psychopathology at enrollment. We focused on at-risk participants. Those with active psychopathology are not at-risk—they have it. Moreover, we felt that it was a matter of safety. Recruiting participants from across the United States restricts the ability of our team to manage or treat an actively depressed mother. Ethically, we believe that we needed to demonstrate that SB can mitigate or prevent PMADs before evaluating whether it can treat active PMADs. However, if a participant develops PMAD at post partum, they will remain in the study and be referred for treatment. To clarify, we are only excluding women with a positive diagnosis of SCID; women with a history of PMAD or who are effectively treated will be included. This decision comes with some concerns. One is that we may have too small of a magnitude or range of mood symptoms to observe a true positive effect of SB on mood symptoms. In other words, the population will be too mentally normal/healthy. We believe, however, that the diverse sample will provide enough variability in mood symptoms, especially since a greater percentage of active-duty women and military spouses experience mental health conditions and at a higher rate than civilians [99-101]. If we notice that the rate of PMAD symptoms is limited or if we are excluding too many participants due to active psychopathology, we may alter the design to include active psychopathology. Another limitation is that the study requires participants to have access to the internet; therefore, individuals of low socioeconomic status and certain racial/ethnic groups may potentially be excluded from the study [102]. However, low-income Americans have made gains in technology and access to the internet, which is likely to continue in the future. A primary goal of this study is to have a diverse sample of racial and ethnic backgrounds. Recruiting and retaining a broad range of participants, particularly those of low socioeconomic status, has been challenging, with recent calls to enhance representation [103,104]. In order to provide an equitable interpretation of the data, the participants need to be diverse and accurately reflect the population of the United States. Therefore, a major emphasis will be on recruiting a diverse and representative sample of military-affiliated participants. Although attrition has been a minimal issue in our studies, we are cognizant of the duration and expectations of the protocol. Thus, our group will maintain regular contact and troubleshoot, if necessary, to enhance retention.

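### The anxiety-disorder exclusion rests on an interview described as covering mood and sleep disorders only, so women with a current anxiety disorder could enter undetected

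*Protocol article*

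**What the plan says.** The protocol article deals with this in five places.

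- **Participants.** One exclusion is "presence of a depressive or anxiety disorder assessed over videoconference". The same clause names the instrument, the SCID, as "Mental Disorders-5-Clinical Version mood disorders section". Separate criteria exclude psychiatric instability and current psychotropic or sleep medication.
- **Telephone Interview and Screening.** "The interview will contain items of the Structured Clinical Interview for Diagnostic and Statistical Manual of Mental Disorders-5-Clinical Version", together with the SCID for sleep disorders. The SCID modules are not named.
- **Table 1, maternal screening measures.** The diagnostic row is the "depression module/sleep SCID". No anxiety module is listed. The GAD-7 is scheduled at baseline and at every postpartum month, but among the primary maternal assessments, not the screening measures.
- **Primary Maternal Assessments.** The GAD-7 and the Perinatal Anxiety Screening Scale "will be used to assess anxiety symptoms over time". Neither is given an eligibility threshold.
- **Limitations.** The trial aims at prevention, not treatment: "Hence, we chose to exclude participants with active psychopathology at enrollment". The section then clarifies that "we are only excluding women with a positive diagnosis of SCID", and that women with past or effectively treated illness are admitted.

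Anxiety is also an outcome. The abstract states: "The primary outcomes for this study will be postpartum mood (depressive and anxiety symptoms) and infant and maternal sleep".

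**The concern.** The criterion names two classes of disorder, and the instrument attached to it is described, twice, by labels that cover one of them. This is more than a detail left to a fuller document. The article chose to state which assessment establishes the exclusion, and the stated scope does not match the condition excluded.

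Two things are at stake. First, the Limitations section rests the prevention rationale on this exclusion, arguing that women with active illness are no longer at risk because they already have it. If anxiety disorder is not assessed at entry, that argument holds for depression only. Second, hypothesis 3a compares immune profiles between women with and without postpartum mood and anxiety disorders (PMADs), starting in late pregnancy, and the immune analysis section speaks of women who go on to develop them. A woman already ill with anxiety at baseline could be placed in that group. Her late-pregnancy sample would then accompany the illness and not precede it.

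**Working it through.** No formula applies, because the point depends on no sample size, error rate or effect size. The check sets the passages side by side.

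1. **What is excluded?** Current depressive disorder or current anxiety disorder (Participants).
2. **What is said to establish it?** The mood disorders section of the SCID-5 (Participants), and the depression module plus the sleep SCID (Table 1). On the article's own labels, neither is an anxiety assessment.
3. **Does another passage supply one?** The telephone-interview section refers to items of the SCID without naming modules, so it neither adds an anxiety module nor rules one out. The GAD-7 is present at baseline, but as a symptom measure with no cutoff for entry. The Perinatal Anxiety Screening Scale does not appear in Table 1.
4. **Does Limitations allow another route to exclusion?** It ties the exclusion to a positive SCID diagnosis. In context, the word *only* mainly contrasts current with past illness, but it points to no second instrument.
5. **Would the analysis make up for it?** Three places were checked.
   - The aim 3 models in Statistical Analyses for Immune Measurements adjust for depressive severity at baseline and psychotropic medication use. The cross-sectional models give gestational age and BMI as example covariates. No baseline anxiety term is named.
   - The list of additional covariates contains no baseline anxiety score.
   - The mixed models under Mean Differences are 2 × 6, while Study Design has seven timepoints: one in late pregnancy and six after delivery. The baseline score therefore does not enter them as a repeated measure. The planned baseline comparison of the arms checks balance and adjusts nothing.

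**Result.** As described, the screening could pass a woman with a current anxiety disorder, and no stated analysis step separates her from a new case.

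The same passages also disagree on mode. Participants has the SCID done by videoconference, while the screening section describes a telephone interview.

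**The case against.** The strongest reply is that this is a condensed article and the telephone-interview section leaves the SCID items open, so an anxiety module may be used in practice. Women also complete a screening survey and baseline questionnaires before the interview, and the exclusions for psychiatric instability and psychotropic medication would remove some cases. This stands in part: the article supports *could enter undetected* and no more. It does not remove the mismatch, because where the article does name the scope, twice, anxiety is outside it. The medication criterion is also a weak filter. An untreated woman passes it, and the article elsewhere stratifies randomization by antidepressant use, adjusts for psychotropic use and admits effectively treated women.

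A second reply is that randomization protects the main comparison. That stands in full. Undetected baseline anxiety is expected to be balanced between the arms and does not bias the smart versus traditional bassinet contrast. Anxiety is analysed as symptoms over time, not as incident diagnosis, and the stated goal includes reducing recurrence.

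A reader might go further and infer that such women do enter, or that they form a large part of the PMAD group. The documents support neither. They give no prevalence of anxiety disorder in pregnancy. If 5% to 15% is assumed, 342 × 0.05 = 17 and 342 × 0.15 = 51 women. At the article's PMAD rates of 12.2% and 26% there would be 342 × 0.122 = 42 and 342 × 0.26 = 89 cases. The ratio then runs from 17/89 = 19% to 51/42 = 121%, which is impossible for a share. The exercise also ignores the other exclusions, assumes that every case persists and is counted as PMAD, and applies background rates to a screened sample. It should not be used as a size. Nor is there a basis for saying that the screening misses a particular fraction of what it should exclude.

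**Conclusion.** The point holds as an internal contradiction about eligibility with a limited statistical consequence. The article excludes current anxiety disorder but describes no assessment that would establish it, so affected women could enter undetected. Their number cannot be derived.

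The consequence has three parts:

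- The randomized arm comparison is not biased.
- The statement that active psychopathology is excluded, and any claim to prevent anxiety disorder as opposed to lowering anxiety symptoms, is not supported as written.
- The non-randomized comparison in hypothesis 3a could mix prevalent with new cases, and its stated adjustment addresses baseline depression but not baseline anxiety.

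This rests on two assumptions: that the labels in Participants and Table 1 describe the modules actually used, and that anxiety counts toward the PMAD grouping. The second follows from the name of the construct and from the use of GAD-7 next to the Edinburgh scale in the immune analyses, although the article gives no case definition. Figure 1 could not be read and may hold more detail. The point should be corrected, but it does not threaten the main contrast.

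**What to change.** 1. **Reconcile the text.** Bring Participants, Telephone Interview and Screening, Table 1 and Limitations into agreement. Either the stated assessment covers every disorder said to be excluded, or the exclusion and the description of the sample are restated to match the assessment actually done. Which of these applies is for the investigators. The mode of interview should be made consistent at the same time.
2. **Add baseline anxiety to the aim 3 models.** Include the baseline GAD-7 score next to baseline depressive severity. Adjust for it as well wherever GAD-7 is analysed as an outcome. The listed models do not name a separate anxiety model, so this should be stated for whichever analysis carries it.
3. **Add a sensitivity analysis for hypothesis 3a.** Set apart women with elevated baseline GAD-7, using a cutoff specified before analysis, and report whether the immune differences remain among the others.

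The cost is protocol wording, one covariate already collected and one further analysis, with no added burden on participants. The sensitivity analysis will have fewer PMAD cases and less precision. The GAD-7 measures symptoms and is not a diagnosis, so it limits the problem without replacing a diagnostic assessment. This matters for women enrolled since recruitment began in January 2025, if anxiety was not assessed at their screening. If the exclusion is restated as depressive disorder only, the prevention claim for anxiety becomes narrower.
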